**Figure 1 F1:**
[figure not shown]
The study flow diagram. ^∗^The number of participants expected to complete this trial.

**Table 1 T1:**
[figure not shown]
The schedule of enrollment, interventions, and assessments.

### Interventions

2.4

The investigational product will be provided by COSMAX BIO Inc. (Jecheon, Chungcheongbuk-do, Republic of Korea). The active product is a 500 mg tablet containing 250 mg of HT080 (60 mg of *C cassia* extract and 190 mg of *R laevigata* extract). To ensure blinding, the placebo tablet will be of the same size, shape, and color as the active tablet. Participants will be orally administered 2 active or placebo tablets twice daily (morning and evening before meals) for 12 weeks. HT080 will be administered at a dose of 1000 mg daily. The investigational product will be packaged as a 6-week supply and will be prescribed to participants at baseline and week 6. To improve the adherence to the treatment, participants will be encouraged to adhere to the prescribed dosage regimen, and compliance will be evaluated by counting the number of unused tablets returned at 6 and 12 weeks.

The following treatments will be prohibited during the trial period: drugs such as 5α-reductase inhibitors and α-blockers administered for BPH, drugs administered for nocturnal enuresis or erectile dysfunction, antimuscarinic agents and supplements for prostate health, and procedures such as transurethral needle ablation, prostatectomy, and laser treatment. Intake of functional foods and medications administered before study participation and agents that are not expected to affect the trial results may be permitted at the investigator's discretion. Drugs used for short-term treatment of other diseases will be co-administered after consultation with the investigator. Participants will be instructed to continue their usual dietary pattern and physical activity habits during the trial period and avoid the consumption of products containing *C cassia* and/or *R laevigata*. Concomitant medications and therapies will be monitored at 6 and 12 weeks.

Criteria for discontinuing intervention will include the following:1.violation of inclusion or exclusion criteria,2.detection of a systemic disease that had not been identified during participant screening,3.discontinuation of participation following notice of withdrawal by the participant or his/her legal representative because of unsatisfactory trial results or adverse events during the study period,4.withdrawal of consent to participate,5.loss to follow-up,6.difficulty with administration of the investigational product,7.intake of other medications, such as 5α-reductase inhibitors, α-blockers, and antimuscarinics that could affect the results of this trial, and (8) trial discontinuation is deemed necessary by the investigator.

### Randomization and blinding

2.5

Eligible participants will be randomized in a double-blind fashion to HT080 or placebo (1:1 ratio) using a block randomization method. The randomization sequence number will be generated by an independent statistician using the SAS system (SAS Institute Inc., NC). Participants will be assigned a randomization number based on the order of enrollment and will receive the investigational product labeled with the corresponding randomization number during the study period. Block size will not be disclosed to the research personnel for allocation concealment. Packaging of the active product and the placebo will be identical to maintain double-blinding. The randomization sequence will be sealed in opaque envelopes and will not be disclosed until the end of the study, except for cases in which participants develop serious adverse events (medical emergencies). If the investigator concludes that it is necessary to break the code, he/she will notify the contract research organization and the study sponsor regarding premature unbinding, and they will discuss and decide together whether the situation warrants breaking the code. In cases of a code break, the date and reason will be recorded in the case report form, and the corresponding participant will discontinue the study.

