### Data management and monitoring

2.9

To ensure data quality, regular monitoring by a contract research organization will be conducted in compliance with standard operating procedures until the end of the study. Experienced clinical research associates will verify source documents and case report forms. All documents related to this trial will be kept confidential in a separate facility, and access to the documents will only be allowed for the purposes of trial management. Data quality will be promoted using double data entry and range checks for data values. A data monitoring committee will not be necessary because the study product is low-risk and no interim analyses will be performed. Auditing is not scheduled for this study.

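### In a medical emergency, section 2.5 makes opening a participant's code depend on agreement with the CRO and sponsor, even after the investigator has judged it necessary

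*Protocol article*

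**What the plan says.** The code-break rule stands in section 2.5 (Randomization and blinding) of the protocol article and has four parts.

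- **Storage.** "The randomization sequence will be sealed in opaque envelopes".
- **Exception.** The sequence "will not be disclosed until the end of the study, except for cases in which participants develop serious adverse events (medical emergencies". No other ground for early disclosure is named.
- **Authorisation.** "If the investigator concludes that it is necessary to break the code", then "he/she will notify the contract research organization and the study sponsor regarding premature unbinding" (unblinding is evidently meant), and "they will discuss and decide together whether the situation warrants breaking the code".
- **Consequence.** After a break, "the date and reason will be recorded in the case report form, and the corresponding participant will discontinue the study".

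Section 2.10 (Harms) covers the handling of serious adverse events, and sections 2.4 (Interventions) and 2.11 (Withdrawal and dropout) cover discontinuation and withdrawal. None of the three mentions opening the code.

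**The concern.** An emergency exception to blinding lets the treating physician learn what a participant has been taking when that knowledge bears on care. Section 2.5 grants the exception but attaches a procedure that weakens it. The investigator's conclusion that a break is necessary only starts a discussion, and the question of whether to break the code is then settled by three parties, two of which are not treating the participant.

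This goes beyond a duty to inform. A notification duty would leave the decision with the investigator. Here the decision is shared and comes before the break, so the CRO or the sponsor could hold it up or not agree to it. At stake is the safety of the individual participant in an emergency where the allocation matters.

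**Working it through.** The point has no arithmetic of its own. The check is a reading of section 2.5 in order, followed by a search for another route to the allocation.

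**Step 1: when may the code be opened early?** Only for serious adverse events, glossed as medical emergencies.

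**Step 2: what starts a break?** The investigator concludes that it is necessary. The person at the bedside has by then already made the clinical judgement.

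**Step 3: is that conclusion enough?** No. The CRO and sponsor are notified, and all three then decide whether the situation warrants the break. The word *whether* leaves room for the answer no.

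**Step 4: to which cases does the joint step apply?** Step 1 admits only emergencies, so the joint step applies to those. Nothing in section 2.5 reserves it for less urgent requests.

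**Step 5: is there another route to the allocation?**

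| Section | What the investigator can do alone | Gives the allocation? |
|---|---|---|
| 2.4 Interventions (discontinuation criteria) | Discontinue where the investigator deems it necessary; a participant may also leave because of adverse events | No |
| 2.10 Harms | Judge severity and causality, report a serious adverse event to the review board, decide whether the trial continues or stops | No |
| 2.11 Withdrawal and dropout | Withdraw a participant for medical reasons, including adverse events | No |

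The investigator can therefore act on the participant's treatment and report the event without anyone's agreement, but cannot learn the allocation that way. There is also an imbalance: section 2.10 leaves to the investigator whether the whole trial continues, while section 2.5 does not let the same person open one participant's code alone.

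**Step 6: does this touch the design figures?** No. Section 2.7 uses a difference of 1.18, a standard deviation of 1.88, a two-sided 5% level and 80% power. By the normal approximation, n per group = 2 × (1.960 + 0.842)² × 1.88² / 1.18² = 39.9, rounded up to 40. That gives 80 in total, and 80 / (1 − 0.20) = 100 enrolled, as stated. The code-break rule enters none of these inputs. A participant whose code is broken leaves the study, but this would count against the 100 − 80 = 20 places already allowed for dropout.

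**The case against.** The strongest reply is that section 2.5 is coherent. One sentence says when early disclosure is possible and the next says how it is authorised. That is correct: a condition followed by its procedure is not a contradiction, and a reader who infers one goes too far. What remains is that the procedure chosen does not suit the only condition to which it applies.

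A second reply is that the joint step may have been meant for non-emergency requests. The text names no such requests, so this reading has no support as printed. If it was the intention, the rewording below would simply make it explicit.

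Four stronger readings are tempting, and the document supports none of them.

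- *That this is the only safeguard for an individual participant.* It is not. Sections 2.4, 2.10 and 2.11 allow discontinuation, withdrawal and reporting without unblinding. It is the only stated route to the allocation.
- *That the delay has no limit.* Section 2.5 gives no time limit, contact arrangement or envelope custodian. A journal article commonly leaves such details to the full protocol, which section 2.12 says exists and is not published. Their absence proves nothing. The point rests on the joint decision that was printed.
- *That the discussion unblinds the sponsor.* It takes place while the code is still sealed, so it cannot itself reveal the allocation, and the text does not say that the sponsor or CRO is told the result. Any disclosure would concern one participant, who then leaves the study.
- *That the lack of independent oversight makes this worse.* Section 2.9 states: "A data monitoring committee will not be necessary because the study product is low-risk". Nothing in the article would give such a committee a part in a single emergency code break, so its absence has no bearing here.

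It is also fair to say that delay or refusal is something the rule permits, not something the text predicts.

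**Conclusion.** The point holds as a badly fixed rule. As written, the CRO and sponsor share the decision on whether the allocation is disclosed in a medical emergency, after the investigator has already found disclosure necessary, and no other section offers a way to obtain it.

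The practical size is small in frequency, because few such events would be expected among 100 men; the article gives no event rate from which to compute a number. The rule would nevertheless apply to each emergency in which a break was sought. The consequence is for individual safety, with no effect on sample size, power or the significance level.

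The conclusion assumes that section 2.5 reflects the operative procedure. If the full protocol already lets the investigator open the code alone in an emergency, the article misstates it and the wording still needs correcting. The change is cheap enough that it should be made.

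**What to change.** Reword the authorisation sentences of section 2.5 to separate two cases.

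1. **Medical emergency.** The investigator may open that participant's code without prior agreement, and afterwards notifies the CRO and sponsor that a break has occurred, without stating the allocation. The existing requirement to record the date and reason stays.
2. **Any other request.** The joint discussion and decision apply as now written.

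A cross-reference from section 2.10 would show which rule applies when a serious adverse event occurs.

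The cost is a few sentences, plus making sure that an individual participant's code can be reached by the investigator without opening the rest of the sequence. The article does not say who holds the envelopes, so this may already be so. The downside is a slightly greater chance of an unnecessary code break, each of which takes a participant out of the study under the present rule. Section 2.1 reports that no participant had been enrolled at the time of writing, so at that stage the change could be made before anyone was exposed.

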### Outcome measures

2.6

The Korean IPSS questionnaire will be used to assess the primary endpoint. The IPSS, which has been used for decades to assess the severity of LUTS/BPH, contains seven questions on voiding symptoms (incomplete emptying, intermittency, weak stream, and straining) and storage symptoms (frequency, urgency, and nocturia).^[22]^ Each item is scored 0 to 5, giving a maximum total score of 35. A total score of 0 to 7 indicates mild symptoms, 8 to 19 indicates moderate symptoms and 20–35 indicates severe symptoms. Participants will complete the IPSS questionnaire at screening, baseline, and weeks 6 and 12. The primary efficacy endpoint is the change in IPSS at week 12 from the baseline.

As the secondary outcomes, uroflowmetry parameters (maximal urinary flow rate and post-void residual volume) and serum prostate-specific antigen, testosterone, and dihydrotestosterone levels will be measured at screening and weeks 6 and 12. Global response assessment will be completed by participants at weeks 6 and 12 using a five-point scale (markedly worsened, worsened, unchanged, improved, and markedly improved). It has been reported that 70% of BPH patients has an associated erectile dysfunction.^[23]^ Participants will complete the International Index of Erectile Function questionnaire, a multi-dimensional self-report instrument widely used to evaluate male sexual function,^[24,25]^ at baseline and weeks 6 and 12. The safety outcome measures include adverse events, laboratory tests (hematology, biochemistry, and urinalysis) results, vital signs, and physical examination.

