### Procedures

2.3

This trial is designed to provide treatment with either HT080 or placebo in subjects with LUTS/BPH and assess symptom improvement during 12 weeks of treatment. The flow diagram is shown in Figure 1 and the schedule for enrollment, interventions, and assessment of this study is summarized in Table 1. The principle investigator will obtain written informed consent from subjects who voluntarily agreed to participate in this trial before eligibility assessment. After applying inclusion and exclusion criteria, eligible participants will undergo baseline assessments within 14 days of screening visit. Following the administration of HT080 or placebo, participants will visit the hospital at weeks 6 and 12 (visit window ± 7 days) and evaluated for efficacy and safety of the investigational product as shown in Table 1. A 24-hour dietary recall questionnaire will be used on 3 random days during the last week of each time point at baseline and at weeks 6 and 12 to investigate participants’ usual dietary pattern during the trial.

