### Sample size

2.7

This trial aims to determine whether HT080 is superior to placebo for reducing the change in IPSSs from baseline to week 12. The sample size has been estimated based on the results of a previous study that had shown an extract of *Ganoderma lucidum* improves IPSSs.^[26]^ Because the standard deviations for changes in IPSSs are not present in this literature, they have been approximated using the confidence intervals and significant probabilities of pre- and post-treatment values for IPSSs. The difference in the mean change in IPSSs between the HT080 and control groups is hypothesized to be 1.18 and the standard deviation is hypothesized to be 1.88. A total of 80 participants, 40 in each group, are required to achieve 80% power with a two-sided significance level of 5%. Considering a dropout rate of 20%, a total of 100 participants (50 in each group) will be enrolled.

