### Statistical analysis

2.8

Efficacy outcomes will be assessed in both full analysis and per-protocol sets. The full analysis set will consist of all randomized participants who are subjected to at least one efficacy evaluation after being administered at least one dose of the study product without failing major inclusion criteria. The per-protocol population will include participants in the full analysis population who complete this trial without major protocol deviations that affect the study results. Safety outcomes will be analyzed in the safety set, which will include all randomized participants who receive at least one dose of study product. Missing values will be handled by the last observation carried forward method.

Continuous variables will be presented with mean, median, standard deviation, and range (min and max), and categorical variables will be presented as frequency and percentage. Continuous variables between the two groups will be compared by the two-sample *t* test or Wilcoxon rank sum test, depending on the normality of distribution, and the differences before and after treatment in each group will be analyzed using a paired t-test or Wilcoxon signed-rank test. Categorical variables will be compared using the chi-square test or Fisher exact test. For primary and secondary efficacy variables, analysis of covariance will be performed to compare the change from baseline to weeks 6 and 12 between the groups while adjusting for baseline values. If necessary, subgroup analysis stratified by baseline characteristics (e.g., age) will be performed. Adverse events will be coded by System Organ Class and Preferred Terms from the Medical Dictionary for Regulatory Activities. Probability values of <.05 with two-tailed tests will be considered significant. The statistical analysis will be performed with SPSS Statistics software version 25 (IBM, Chicago, IL). There will be no interim analyses.

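### The screening IPSS has no stated place in the primary ANCOVA; adding it as a second covariate would probably gain a few percent in precision

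*Protocol article*

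**What the plan says.** Outcome measures: "Participants will complete the IPSS questionnaire at screening, baseline, and weeks 6 and 12". The same section defines the endpoint: "The primary efficacy endpoint is the change in IPSS at week 12 from the baseline". It lists screening and baseline as distinct occasions.

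Procedures: "eligible participants will undergo baseline assessments within 14 days of screening visit". Study product is given only after that, so both readings are untreated and close together in time.

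Statistical analysis: for the primary and secondary efficacy variables, ANCOVA will "compare the change from baseline to weeks 6 and 12 between the groups while adjusting for baseline values". No role in the analysis is stated for the screening IPSS; its apparent use is the entry criterion of 8–19 under Eligibility criteria. The same section also plans an unadjusted comparison: "Continuous variables between the two groups will be compared by the two-sample *t* test or Wilcoxon rank sum test". It does not say which of the two is primary.

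Sample size: "The difference in the mean change in IPSSs between the HT080 and control groups is hypothesized to be 1.18". The SD of the change is taken as 1.88. Together these lead to 40 men per group for 80% power at two-sided 5%, and to 100 enrolled after 20% dropout. No credit is taken for covariate adjustment.

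**The concern.** A single questionnaire score carries measurement noise. A second untreated reading of the same score can sharpen the adjustment for where each man started, and so reduce the residual variance of the treatment comparison. Here the second reading is already collected from every man, and the stated model does not use it. The Discussion names the small sample as a limitation, and the Sample size section says that the SD had to be approximated because the source study did not report it. Precision that needs no extra patient, visit or questionnaire is therefore worth having. At stake is a modest amount of power on the primary comparison. Validity and bias are not in question.

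**Working it through.** **The plan's own figure.** With difference 1.18 and SD 1.88 (Sample size), n per arm = 2 × (1.960 + 0.842)² × (1.88/1.18)² = 39.8, so 40. Normal-approximation power at 40 per arm is 80.2% (79.2% with the exact t distribution). Allowing for dropout, 80/(1 − 0.20) = 100. The stated figures reproduce.

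**Set-up.** Let b be the correlation of baseline with week-12 IPSS, s that of screening with week-12 IPSS, and q that of screening with baseline IPSS. None of these is in the article; all values below are assumptions. ANCOVA of change adjusted for baseline gives the same treatment estimate as ANCOVA of the week-12 score, so:

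- Baseline alone: R² = b².
- Baseline and screening as separate covariates: R² = (b² + s² − 2bsq)/(1 − q²). If s = b = r, this becomes 2r²/(1 + q).
- Ratio of residual variances = (1 − R² with both)/(1 − b²).
- The extra covariate costs about 1/76 = 1.3% of variance at 80 men (factor 77/76).
- To stay on the plan's scale, the SD of change is held at 1.88. With equal variances at baseline and week 12, σ = 1.88/√(2(1 − b)), and the residual SD is σ√(1 − R²). Power = Φ(1.18/(SD × √(2/40)) − 1.96).

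Screening adds information only so far as s departs from b × q. At s = bq it adds nothing.

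**Results.** The power columns do not charge the lost degree of freedom; the net column does.

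| b | s | q | R² baseline | R² both | Fall in residual variance | Net of 1 df | Power, baseline only | Power, both |
|---|---|---|---|---|---|---|---|---|
| 0.5 | 0.5 | 0.5 | 0.250 | 0.333 | 11.1% | 9.9% | 90.0% | 93.0% |
| 0.5 | 0.5 | 0.8 | 0.250 | 0.278 | 3.7% | 2.4% | 90.0% | 91.0% |
| 0.5 | 0.5 | 0.9 | 0.250 | 0.263 | 1.8% | 0.5% | 90.0% | 90.5% |
| 0.6 | 0.6 | 0.6 | 0.360 | 0.450 | 14.1% | 12.9% | 88.1% | 92.3% |
| 0.6 | 0.6 | 0.8 | 0.360 | 0.400 | 6.2% | 5.0% | 88.1% | 90.0% |
| 0.6 | 0.6 | 0.9 | 0.360 | 0.379 | 3.0% | 1.7% | 88.1% | 89.0% |
| 0.6 | 0.57 | 0.8 | 0.360 | 0.382 | 3.5% | 2.2% | 88.1% | 89.2% |
| 0.6 | 0.55 | 0.8 | 0.360 | 0.374 | 2.1% | 0.8% | 88.1% | 88.7% |
| 0.6 | 0.5 | 0.8 | 0.360 | 0.361 | 0.2% | −1.1% | 88.1% | 88.1% |

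Worked example, last row: R² = (0.36 + 0.25 − 0.48)/(1 − 0.64) = 0.13/0.36 = 0.361, and the variance ratio is 0.639/0.640 = 0.998. Here bq = 0.48, so s = 0.5 leaves almost nothing to add.

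**Range restriction.** A simulation restricted screening IPSS to 8–19, with an assumed unrestricted mean of 14–16 and SD of 5–6, b = s between 0.5 and 0.8, and q equal to that value or higher by 0.1 to 0.2. Residual variance fell by about 3% to 14%. Equal correlations of 0.7–0.8 give a fall of 17–20% without the restriction, but about 8–14% with it. The simulated SDs of change (3.2 to 6.0) are well above the plan's 1.88, so only the variance ratios are used.

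**Averaging the two scores.** The mean correlates ((b + s)/2)/√((1 + q)/2) with week 12. At 0.6, 0.5 and 0.8 this is 0.55/√0.9 = 0.580, so R² = 0.336, below the 0.360 from baseline alone. Residual variance is then 0.664/0.640 = 1.037 times as large, a rise of about 4%. The mean matches two separate covariates when s = b, but it can do harm when screening predicts less well.

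**The case against.** The strongest objection is that nothing here is wrong. Baseline-adjusted ANCOVA is standard and valid, the sample size stands, and a further covariate is a choice that a full protocol or SAP, neither of which is shown, might already make. The reference to baseline values does not expressly exclude the screening score. This stands against any claim of error, and against reading the article as a decision to discard the screening score. It does not remove the suggestion: the article does state its model, screening is listed separately from baseline, and the change is specific and nearly free.

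The second objection is to the size. A reader might infer an assured gain of 4% to 14%. That range requires screening IPSS to predict week 12 as well as baseline IPSS does. Its upper end also requires two untreated readings at most 14 days apart to be no more alike than readings 12 weeks apart across treatment. The screening score is earlier and, if it is the qualifying score, restricted to 8–19, so its correlation with week 12 may well be lower. With 0.6, 0.5 and 0.8 the gain is nil and the lost degree of freedom makes it slightly negative. This objection stands, and the lower part of the range is the more realistic.

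Third, the gain arises only if ANCOVA is the primary test. The article also lists a t test or Wilcoxon test without ranking them, so the benefit is conditional on settling that.

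**Conclusion.** The point holds as a small efficiency gain. Two pre-treatment IPSS readings are collected and only baseline is named as covariate. Using screening as a separate second covariate would cut residual variance by roughly 0% to 14%, most likely a few percent, and raise power at 40 per arm by about 0 to 4 points, before about 1% of variance is given back for the degree of freedom. These figures rest on assumed correlations, on the plan's SD of 1.88 and on ANCOVA being primary.

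A reader might infer that the trial is underpowered or its analysis flawed without this change. The documents do not support that: the stated 80% power reproduces without any adjustment, and under the assumptions above baseline-only ANCOVA already gives about 88% to 90%. Nor is averaging the two readings a safe equivalent, since it can raise residual variance by about 4%.

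**What to change.** In Statistical analysis, prespecify ANCOVA of the change in IPSS from baseline to week 12 as the primary analysis, with treatment, baseline IPSS and screening IPSS as separate terms. Do not replace the two scores by their mean. Keep the endpoint as change from the baseline visit: the screening score, if it is the qualifying one, is range-restricted and prone to regression to the mean, so it belongs in the model only as a covariate.

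The cost is one more model term and one degree of freedom. No new data, visits or patients are needed, and the sample size need not change. The article reports that nobody had yet been enrolled, so the covariate could be fixed in advance; added after unblinding it would look data-driven.
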